## Abstract

**Background:**

Latent inhibition occurs when exposure to a stimulus prior its direct associative conditioning impairs learning. Results from naturalistic studies suggest that latent inhibition disrupts the learning of dental fear from aversive associative conditioning and thereby reduces the development of dental phobia. Although theory suggests latent inhibition occurs because pre-exposure changes the expected relevance and attention directed to the pre-exposed stimulus, evidence supporting these mechanisms in humans is limited. The aim of this study is to determine if two variables, *pre-exposure session spacing* and *multiple context pre-exposure*, potentiate the hypothesized mechanisms of expected relevance and attention and, in turn, increase latent inhibition of dental fear.

**Methods:**

In a virtual reality simulation, child and adult community members (ages 6 to 35) will take part in pre-exposure and conditioning trials, followed by short- and long-term tests of learning. A 100ms puff of 60 psi air to a maxillary anterior tooth will serve as the unconditioned stimulus. Pre-exposure session spacing (no spacing vs. sessions spaced) and multiple context pre-exposure (single context vs. multiple contexts) will be between-subject factors. Stimulus type (pre-exposed to-be conditioned stimulus, a non-pre-exposed conditioned stimulus, and an unpaired control stimulus) and trial will serve as within-subject factors. Baseline pain sensitivity will also be measured as a potential moderator.

**Discussion:**

It is hypothesized that spaced pre-exposure and pre-exposure in multiple contexts will increase the engagement of the mechanisms of expected relevance and attention and increase the latent inhibition of dental fear. It is expected that the findings will add to theory on fear learning and provide information to aid the design of future interventions that leverage latent inhibition to reduce dental phobia.

## Introduction

Dental phobia, a persistent and excessive fear of dental stimuli and procedures that results in avoidance or distress, represents a significant barrier to children and adult oral health [1]. Dental anxiety correlates positively with disadvantageous oral health behaviors and outcomes, including less frequent dental care visits [2, 3], lack of adherence to dentist advocated treatment [4], and increased likelihood of tooth decay, missing teeth, and periodontal diseases [5–7]. Dental fear and anxiety relate to poor oral health, which in turn, may increase the risk for heart disease, stroke, diabetes, and poor quality of life [8–10]. As marginalized individuals in the United States (including African American and Hispanic individuals) are particularly burdened by dental anxiety and problems of oral health, the study of dental anxiety has broad societal significance [11, 12].

Research suggests that direct associative conditioning is often responsible for the development of dental fear [13–15]. That is, an individual who undergoes an uncomfortable or painful dental procedure (unconditioned stimulus) may form an association between the dentist and/or dental-related stimuli (the conditioned stimulus) with fear (the conditioned response). In subsequent situations, such as future dental consultations, the dentist and/or dental related stimuli will then elicit the conditioned response.

Although experiencing painful or distressing dental events increases the likelihood of dental anxiety, this associative conditioning effect does not always occur. Research suggests that the experience of non-painful or non-traumatic dental events prior to negative dental experience(s) decreases the probability of enduring dental anxiety from associative conditioning [13, 14]. That is, pre-exposure to the dentist or dental related stimuli (e.g., office, chair, instruments) in the absence of a negative experience may reduce the likelihood of developing dental phobia. This impairment of associative learning from non-reinforced stimulus pre-exposure is a phenomenon labeled latent inhibition (LI). In LI, previous uneventful stimulus exposure reduces one’s ability to subsequently acquire or express a new association with that stimulus [16, 17].

It may be possible to strategically leverage the LI effect to help prevent the formation of dental phobia. To design effective interventions, however, it is critical to understand the mechanisms underlying LI of dental fear. This knowledge would allow for the creation of maximally efficient LI interventions—ones that generate clinically meaningful effects. As such, our team initiated a program of research to clarify the mechanisms underlying the LI of dental fear in humans. This work is grounded in the Hall and Rodríguez model of LI [18], which proposes expected relevance (i.e., prediction errors) and attention as mechanisms responsible for LI. According to this model, novel stimuli have high informational value and as such, they attract attention. When a novel stimulus is presented without an unconditioned stimulus (UCS), the heightened attention increases the likelihood the individual will learn a “stimulus → no event” association. When exposure to the stimulus continues without a UCS, the individual is said to receive further evidence for this stimulus → no event association. Over time, one learns that the pre-exposed stimulus is a signal with little informational value, and attention is therefore diverted elsewhere. When the stimulus is later paired with a UCS, the lack of attention hampers the associability potential of that pre-exposed stimulus, thereby resulting in LI.

Our team is testing the potential mediating role of expected relevance and attention in the LI of dental fear as proposed by the Hall and Rodríguez model of LI [18]. The present study will add to this line of investigation by experimentally testing if theoretically meaningful changes to pre-exposure modulate the mechanisms of expected relevance and attention, and in so doing change LI. Specifically, here we will investigate the variables of *multiple context pre-exposure* and *pre-exposure session spacing*. In terms of multiple context pre-exposure, presenting the pre-exposed stimulus with more than a single set of cues or settings should serve as a signal that the pre-exposed stimulus → no event association generalizes across contexts. This new learning should further decrease the associability of a stimulus, as this experience extends the initial learning to show the lack of stimulus relevance is not situation specific. Thus, context change should further reduce the expected relevance and attention to the pre-exposed stimulus, and therefore strengthen LI. Pre-exposure session spacing refers to temporally separating pre-exposure into discrete sessions. This spacing can be likened to a type of context change, a temporal change, and for the reasons just described should also decrease expected relevance and attention and thereby increase LI.

Prior studies are consistent with the perspective that pre-exposure spacing and pre-exposure occurring in multiple contexts changes LI. For example, animal studies and studies outside of the dental context, find that when pre-exposure occurs in multiple contexts, it can reduce fear at test and its return following extinction, as well as increasing the effectiveness of LI across contexts [19–21]. Animal studies also show that pre-exposure session spacing reduces fear learning and the context specificity of LI [19].

In addition to manipulating pre-exposure session spacing and context change, we will also test for moderation by individual differences in pain sensitivity. Prior research suggests that individual characteristics which rouse greater attention to a stimulus during pre-exposure should potentiate LI [22]. In the context of fear conditioning with an aversive UCS, pain sensitivity is such a variable [23].

## Research hypotheses

The proposed experiment will assess if pre-exposure session spacing and pre-exposure in multiple contexts potentiate changes in expected relevance and visual attention to the pre-exposed stimulus, and LI of dental fear. Pain sensitivity will also be measured to test if this variable moderates the influence of the proposed mediators on LI.

### Hypothesis 1

Spaced pre-exposure sessions, compared to no spacing, will (a) increase engagement of the proposed mechanisms (expected relevance and attention), and (b) enhance LI of conditioned fear acquisition, recall, and retention.

### Hypothesis 2

Multiple context pre-exposure, as compared to pre-exposure in a single context, will (a) lead to stronger engagement of the proposed mechanisms (expected relevance and attention), and (b) enhance LI of conditioned fear acquisition, recall, and retention.

### Hypothesis 3

Greater pain sensitivity will be associated with increased engagement of the proposed mechanisms of expected relevance and attention and increased LI.

## Methods

### Study participants

Participants will be 180 community volunteers between the age of 6 and 35, with this sample size based on an a priori power analysis for Hypotheses 1 and 2. The power analyses for Hypotheses 1a and 2a were focused on the simple pre-exposure-by-trial interaction for the conditioning and test phases. For the conditioning phase, use of G*power indicated a sample size of 19 is needed to detect a large effect, as suggested by our pilot study, (*f* = 1.3, α = 0.05, power = 0.80) whereas a sample size of 134 is needed for a given test phase to detect a small-to-moderate interaction (*f* = 0.20, α = 0.05, power = 0.80), where no prior effect size was available. For Hypotheses 1b and 2b, PASS software [24] indicated that a sample size of 106 is needed to achieve 0.80 power to detect an indirect effect equal to 0.15, where the standardized regression coefficient linking the mediator to the outcome is 0.3 and the correlation between the initiating variable and mediator is 0.5, with this correlation suggested by our pilot data.

Participants will be recruited in the regions surrounding the study sites in south Texas and northwest Ohio. It is expected that the study locations will provide the opportunity to recruit both Hispanic and African American participants, individuals that face increased burden from dental anxiety and poor oral health [11, 12]. Prior to entering the study, individuals will be screened using the inclusion/exclusion eligibility criteria displayed in Table 1. Participants will complete two or three in-person visits, depending on experimental condition, scheduled approximately 1 week apart. Participants will receive a $50 gift card for each visit. The Institutional Review Board of the primary institution approved the study.

**Table 1 Tab1:** Exclusion and inclusion criteria

**Participant Exclusion Criteria**
Current injury (including fractures, open cuts, or sores) on their dominant hand
Currently have a cardiovascular disorder or a pacemaker
Currently have a seizure disorder or epilepsy
Fixed dental or orthodontic appliance that would interference with fabrication of a mouthpiece
Are colorblind
Currently on any anti-depressant or anti-anxiety medications
Currently have an inner ear infection
Living in the same household or an immediate family member of a participant enrolled in this or prior studies in this series
Unwilling to remove facial cosmetics or attend sessions without facial cosmetics on
Currently have glasses or use contact lenses with a vision correction of ≥ ± 6
History of sensitivity to extreme cold or frostbite
Bleeding disorder or take blood thinners
Vasospastic disorder such as Raynaud’s disease or Raynaud’s syndrome
Gastrointestinal or vestibular disorders that may elevate susceptibility to nausea and dizziness such as hyperemesis gravidarum, Meniere’s disease, or severe migraines
Behavioral, developmental, or sensory disorder that would increase discomfort or ability to complete study tasks
Medical condition that requires them to avoid mild stress
Diagnosis of Temporomandibular Disorder along with a history of exacerbation of symptoms resulting from routine dental procedures
Prior negative outcome with virtual reality simulation
Any medical condition that elevates risk of falls, nausea, dizziness, or causes vasovagal reactions
Any other oral or general health concerns
**Participant Inclusion Criteria**
Be between the ages of 6 and 35 years old
At least 2 of their maxillary anterior 6 teeth present
All of their maxillary anterior 6 teeth are free of hypersensitivity to pressure or pain
All of their maxillary anterior 6 teeth are stable
All of their maxillary anterior 6 teeth are free of cavities
Able to read, write, and converse in English (English or Spanish at UTRGV site)
Willing and able to provide a signed and dated informed consent/assent form to participate
Willing and available to comply with all study procedures and available for the study duration

### Design

The experiment employs a mixed research design, with two within-subject independent variables, two between-subjects independent variables, and one measured continuous variable. The within-subjects variables are stimulus type [stimulus type: pre-exposed to-be conditioned stimulus (CS^+^ _P_), non-pre-exposed to-be conditioned stimulus (CS^+^ _NP_), and an unpaired control stimulus (CS^−^)] and time [trial number]. The between-subjects variables are pre-exposure session spacing [no spacing vs. session spacing] and pre-exposure context [single context vs. multiple contexts]. Pain sensitivity will serve as a continuous moderator variable.

### Procedure

Individuals interested in the study will complete screening and screening consent on the phone or in a virtual meeting. Adults will screen for themselves, whereas a parent or legal authorized representative will screen for children and adolescents. Those qualifying after the screening of inclusion/exclusion factors will be scheduled for the first study session, with subsequent sessions occurring approximately one week apart from each other (min = 7 days). As described below, the number of sessions depends upon pre-exposure spacing condition.

At the start of session 1, participants will re-confirm eligibility, be provided a tablet device, and go through the informed consent (and assent, if appropriate) process. Parent or legal authorized guardian will provide permission for child and adolescent participants. Participants will then complete a pain sensitivity questionnaire and behavioral assessment of pain sensitivity, as described below. Researchers will then fabricate an individualized dental mouthpiece for the participant, place electrodermal activity electrodes on their hand, and deliver instructions for using the virtual reality set up. Using the randomization feature in REDCap (Research Electronic Data Capture; [25, 26]), participants will then be assigned to one of the four between-subject conditions. Randomization occurs during the first study visit, to maintain allocation concealment [27]. Participants will then begin the fear conditioning experimental task.

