For Hypotheses 1a and 2a, changes expected in the proposed mediators should first be detected in the pre-exposure phase. To test these two hypotheses during the pre-exposure phase, a two-factor repeated measures MANOVA with one-between (pre-exposure group) and one-within-subjects (trial) factor will be run separately for the expected relevance and attention variables. A significant group × trial interaction indicates that mean responses across trials is not the same per group. If the interaction is present, follow-up analyses will focus on examining the plots of the mean change for each group and testing the degree to which the mean change from first to last trial differs between groups. For the conditioning phase, we will conduct a three-way repeated measures MANOVA separately for the two proposed mechanisms. For these models, pre-exposure groups will serve as the between-subjects factor with stimulus and trial being the within-subject factors, and the model will assess the main effects of each variable, as well as all-two-way and three-way interactions. Follow-up analyses depend on the nature of effects that are present (e.g., type of interactions or main effects). We anticipate differences will be larger between pre-exposure groups—predominantly at the early trials for stimulus CS^+^ _P_ —than for the other stimulus conditions. Thus, follow-up analyses will concentrate on the degree to which means differ by pre-exposure group and stimulus type for each trial using a Bonferonni-adjusted alpha, as well as examining plots of the mean response by stimulus type and trial for each pre-exposure group.

Hypothesis 3: Greater pain sensitivity will be associated with increased engagement of the proposed mechanisms of expected relevance and attention and increased LI.

To test the Hypothesis 3, pain sensitivity scores will be entered in the above analyses as a moderating variable. This will be done by testing interactions between pre-exposure and pain sensitivity.

Hypothesis 1b: Spaced pre-exposure sessions, compared to no spacing, will enhance LI of conditioned fear acquisition, recall, and retention. Hypothesis 2b: Pre-exposure in multiple contexts, as compared to pre-exposure in a single context, will enhance LI of conditioned fear acquisition, recall, and retention.

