There are several aspects to the proposed experiment that should be highlighted. First, it is expected that the research will include a diverse range of participants in terms of age (6 to 35) and minority group status (e.g., Black/African American and Hispanic/Latino individuals). This within sample variation should allow for a robust test of the hypotheses and do so with minorities who are most burdened by dental anxiety and oral health problems. Second, the study includes more objective indicators of one mediating variable (attention) and a behavioral indicator of fear learning (e.g., proximity of approach to the alien stimuli) which adds markedly to the other self-report measurements. Additionally, the inclusion of a fear retention test one week later is noteworthy, as many fear conditioning studies do not provide an extended fear assessment. This is a valuable addition that provides useful information for constructing interventions. Finally, the studies will also take a multi-method approach to assessing the role of pain sensitivity in the LI of dental fear.

The study is expected to provide data that will benefit future interventions. If pre-exposure prevention programs can be developed to reduce dental fear learning, it will be important to know whether such interventions will benefit from the inclusion of session spacing and context changes. This experiment, and others that identify strategies to strengthen LI, should be valuable in dampening the direct associative conditioning that causes dental phobia.

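### The listed models have no term for age or site: a loss of precision in the randomised comparisons, but possible confounding of the mediator-to-outcome path and the pain-sensitivity moderator

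*Protocol article*

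**What the plan says.** - **Sample.** Study participants: "Participants will be 180 community volunteers between the age of 6 and 35", recruited around sites in south Texas and northwest Ohio. The language criterion in Table 1 differs by site: "Able to read, write, and converse in English (English or Spanish at UTRGV site").
- **Allocation.** Procedure: at the first visit, through REDCap, "participants will then be assigned to one of the four between-subject conditions". The article neither names nor rules out a stratification factor.
- **Models for Hypotheses 1a and 2a.** The pre-exposure phase uses group and trial. For the conditioning phase, "pre-exposure groups will serve as the between-subjects factor with stimulus and trial being the within-subject factors", with all their interactions.
- **Hypothesis 3.** Pain sensitivity is added to these models through its interaction with pre-exposure. Under Moderator variables, the self-report questionnaire has an adult form from 18 years and a child form from 6 to 17.
- **Hypotheses 1b and 2b.** Path models run from group to the two mediators (first conditioning trial) and on to a fear outcome averaged over recall or retention trials. No covariate is named.
- **Heterogeneity.** The Discussion treats the spread in age and minority status as a strength: "This within sample variation should allow for a robust test of the hypotheses".

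**The concern.** A 6-year-old and a 35-year-old give the same 10-point probability rating and are measured by the same gaze, anxiety, approach-distance and skin-conductance indices. Age could plausibly affect several of these at once, and so could site, through language and population. If neither is modelled, two different things follow.

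Where groups are compared as randomised, the age and site spread goes into the residual and the comparison is less precise than it could be.

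Where the analysis relates one measured quantity to another, randomisation gives no protection. Mediator and outcome can be associated within groups only because both vary with age. The group-to-mediator path is expected to be real (the sample-size section assumes a correlation of 0.5), so a spurious second path can produce a false indirect effect, and the indirect effect is the study's main mechanistic claim. In Hypothesis 3, pain sensitivity is measured rather than assigned. Its questionnaire changes form at 18, so the score is tied to age by construction.

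**Working it through.** **1. The plan's own sample sizes reproduce.** The article says "a sample size of 134 is needed for a given test phase to detect a small-to-moderate interaction" (f = 0.20, α = 0.05, power 0.80). For the repeated-measures MANOVA interaction with k = 4 groups and m = 4 test trials per stimulus:
- s = min(k−1, m−1) = 3; df1 = (k−1)(m−1) = 9; df2 = s(N−k−(m−1)+s) = 3 × 130 = 390; λ = N·s·f² = 134 × 3 × 0.04 = 16.08.
- Power is 0.803 at N = 134 and 0.799 at N = 133. At the planned N = 180 it is 0.92.

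The article also says "a sample size of 106 is needed to achieve 0.80 power to detect an indirect effect equal to 0.15". With b = 0.3 and correlation 0.5, (1.96 + 0.84)² × (1 − 0.3²) / [0.3² × (1 − 0.5²)] = 105.8 with unrounded quantiles, hence 106. No stated N is wrong.

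**2. Randomised comparisons: type I error.** 20,000 simulated studies had 4 × 45 people (180/4, equal allocation assumed) and no true group effect. Half the sample came from each site, with a site effect of 0.8 residual SD. Age was uniform over 6 to 36, with an effect of 0.05 residual SD per year. The four-group test without site or age rejected in 0.050 of studies, so it is valid.

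**3. Randomised comparisons: precision.** If age and site explain a share R² of the variance of the tested score (assumed), adjustment multiplies the standard error by √(1−R²). For 45 v 45 and an assumed d = 0.5, power ≈ Φ(0.5 × √(45/2) / √(1−R²) − 1.96):

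| R² | SE ratio | Power |
|---|---|---|
| 0 | 1.00 | 0.66 |
| 0.10 | 0.95 | 0.70 |
| 0.20 | 0.89 | 0.76 |
| 0.30 | 0.84 | 0.81 |

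This applies to group means at a single trial and to averaged recall or retention outcomes. It does not carry over to change across trials within a person, where a stable additive age or site effect cancels.

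**4. Mediator-to-outcome path.** Take one mediator M and one outcome Y, each with within-group variance 1. Standardised age has coefficient r on both, and M has no effect on Y. Within groups, corr(M, Y) = r². The test of M adjusted for group has 180 − 4 − 1 = 175 degrees of freedom and noncentrality δ = r²√175 / √(1−r⁴). The false-positive rate is about Φ(δ−1.96) + Φ(−δ−1.96):

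| r (assumed) | Spurious b = r² | δ | False positives, age omitted |
|---|---|---|---|
| 0.2 | 0.04 | 0.53 | 8% |
| 0.3 | 0.09 | 1.20 | 22% |
| 0.4 | 0.16 | 2.14 | 57% |

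Simulation gives the same rates, and about 5% in every row once age is in the model. For scale, the planned b is 0.3. If age acts in opposite directions on M and Y, the spurious path is negative and can mask a real one. The plan's models have two mediators and use a bootstrap test of the indirect effect, so these rates illustrate the path and are not exact for the planned test.

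**5. Moderator.** No figure is available. If the effect of pre-exposure varies with age, and pain sensitivity varies with age, a group-by-pain-sensitivity interaction picks up the age difference. No listed term separates the two.

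**The case against.** The strongest reply is that nothing here threatens the randomised design. The planned 180 already gives power 0.92 for the interaction on which the study was sized. The pre-exposure follow-up concerns change from first to last trial, from which stable age and site differences drop out. For these tests, covariates are a choice among valid analyses. That stands, and it confines the loss in the randomised comparisons to precision.

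Three stronger readings are tempting and are not supported:
- **That allocation is unstratified.** The Procedure section is silent, and a condensed article may leave this to the full protocol. It can be asked, not asserted.
- **That chance imbalance confounds the group comparison.** If allocation were unstratified, with 4 × 45 people and a trait present in half of them (both assumed), the focal group would differ from at least one other by 15 percentage points or more in 38% of allocations, and by 20 or more in 18%. Ordinary standard errors already allow for this, as the 0.050 rejection rate shows.
- **That operator or delivery differences between sites cannot be separated from group.** The article documents no such differences. It describes a programmed task and a fixed stimulus, and individuals are randomised to all four conditions with nothing tying condition to site.

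The power argument does not answer the mediation and moderation point. A larger sample makes a confounded path more likely to reach significance. Nor is the omission mere silence: the article sets out the model terms, although a separate analysis plan could still add covariates.

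**Conclusion.** The point holds in a limited form. The models as listed omit age and site. In the randomised comparisons the consequence is lost precision only: the standard error could be 5% to 16% smaller in between-person comparisons if R² is 0.10 to 0.30. In the mediator-to-outcome path and the pain-sensitivity moderation, age or site can confound the result. For the former, the false-positive rate is about 8% to 57% over assumed age effects of 0.2 to 0.4 on both variables, against about 5% after adjustment. The effect sizes, R², d, site split and age distribution are all assumptions, because the article gives none of them. With age effects well below 0.2 the problem would be small. The claim that a varied sample gives a robust test therefore needs age and site in the models, at least for Hypotheses 1b, 2b and 3.

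**What to change.** Prespecify age (continuous) and site as covariates in the MANOVA models for Hypotheses 1a and 2a, the moderation models for Hypothesis 3, and both the mediator and outcome equations of the mediation models for Hypotheses 1b and 2b. In the Hypothesis 3 models, also include the interaction of group with age, since an age main effect alone does not separate age from pain sensitivity as the moderator. State whether the REDCap allocation list is stratified and, if so, include its stratification factors in the models.

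The cost is small. Site is known, and age is already needed to apply the eligibility criterion and to choose the questionnaire form. The price is a few model terms and a few of the 176 between-subject degrees of freedom (180 − 4). No change to the sample size is needed.
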